## Abstract

**Background:**

The COVID-19 pandemic has resulted in a large number of individuals affected by post-COVID syndrome (PCS) and poses significant challenges to healthcare provision. Many PCS patients are left to manage their condition without adequate support. The aim of the LCovB study is to collect data on symptoms (including pre-existing conditions and comorbidities) and the care situation and trajectories of PCS patients. The results will serve to identify key measures for optimizing care.

**Methods:**

Using a mixed-methods approach, the study includes secondary data analyses of routine data of PCS patients from 44 German statutory health insurance companies, a primary survey and semi-structured interviews with selected PCS patients. In addition, the situation of severely ill patients will be assessed through a physician’s visit and questionnaires. Finally, an expert panel with stakeholders from the healthcare sector will examine the study results using the Delphi method to derive recommendations for treatment and optimized care pathways.

**Discussion:**

The LCovB study examines care trajectories to identify gaps and barriers for patients with PCS, aiming to develop evidence-based recommendations and guidelines for care and disease management, supported by an expert panel.

**Trial registration:**

In August 2025, the study was prospectively registered in the German Clinical Trials Register: Module 1 (DRKS00037341), Module 2 (DRKS00037343), Module 3 (DRKS00037344), Module 4 (DRKS00037345).

## Introduction

According to the Robert Koch Institute (RKI), around 39 million people in Germany have been infected with SARS-CoV-2 since the start of the COVID-19 pandemic in March 2020, of which around 188,000 have died (as at 24 May 2025). According to the RKI, the majority of people with a confirmed SARS-CoV-2 infection are considered to have recovered [1]. However, in the first year of the pandemic, some of those infected already showed persistent symptoms of acute infection, or symptoms that appeared as a result of the infection. The symptoms, subsumed under various terms (including long-COVID), were included by the World Health Organization (WHO) in 2021 under post-COVID syndrome (PCS) (U09.9!) in the International Statistical Classification of Diseases and Related Health Problems, 10th Revision (ICD-10). U09.9! stands for “post-COVID-19 condition” for all cases in which another illness/condition is associated with a previous COVID-19 infection. The diagnosis can be assigned if, three months after a presumed or confirmed SARS-CoV-2 infection, symptoms persist or reappear that last at least two months, cannot be explained by another illness and have a relevant impact on the patient's everyday life [2]. Almost all organ systems can be affected; however, according to the S1 guideline, the most common symptoms include fatigue, cognitive impairment, exercise intolerance, dyspnoea, headaches, disorders of the sense of smell and taste, sleep disorders and psychiatric disorders [2]. The pathophysiological mechanisms of post-COVID symptoms are very diverse and have not yet been finally clarified. Studies have discussed various causes, such as immune dysregulation, mitochondrial dysfunction, prothrombotic inflammation and viral persistence [3].

Previous studies on the prevalence of PCS have produced varying results. The Central Institute for Statutory Health Insurance Physician Care in Germany (Zi) stated a prevalence of around 9% for post-COVID (U09.9!) among all COVID-19 cases registered by 2021 in outpatient claims data in Germany [4]. This number probably reflects underreporting in 2021; studies from European countries such as France, Sweden, Spain, Switzerland, Faroe Islands, Italy and Germany, as well as China and the United States of America came up with prevalence rates between 7 and 30% [5–8]. Hospitalized and female patients are at higher risk of developing PCS [9]. An in-depth analysis by the Zi of outpatient care for PCS patients in Germany, based on claims data from the second quarter of 2021, showed that the majority of people affected are aged 45–64. Persons who were treated for previous somatic and mental illnesses in 2020 also had a higher risk of developing a PCS [10].

In addition, PCS patients were mostly treated exclusively by general practitioners (GPs) (76%). GPs are the first point of contact for those affected, yet studies suggest that they sometimes cannot adequately address the complex problems of people affected by PCS and that there are still too few specialized clinics for the referral of post-COVID cases [11–14]. An increased utilization of pulmonologists and cardiologists in the outpatient claims data compared to a control group was also observed [15].

In 2022, PCS patients most frequently underwent a pneumological rehabilitation, with almost half of the rehabilitations being extended beyond the regular duration [16]. Various studies have shown a significant improvement in post-COVID symptoms through rehabilitation services after a severe course of COVID-19 disease [15,17,18]. The common symptom of fatigue can be reduced in a subset through psychosomatic rehabilitation, but a significant proportion of patients still suffer from relevant fatigue on discharge [19]. A problem in rehabilitation is the lack of knowledge about how to handle post-COVID in those patients who had mild infections and how to approach the frequent symptom of post-exertional malaise (PEM) and the subgroup with ME/CFS. This leads to patients feeling stigmatized or that they are not taken seriously [20]. Adapted, symptom-oriented rehabilitation that avoids overexertion and teaches strategies such as pacing is crucial for PCS patients with PEM. Multimodal and interdisciplinary rehabilitation approaches are seen as promising [21].

This is particularly important in the context of avoiding long periods of work disability among the working population. Although rather low absolute numbers of sick leaves due to post-COVID were registered in initial studies, PCS patients were then unable to work for an average of more than 100 days; depending on gender (more women), the severity of the COVID-19 infection previously contracted and the age of those employed. PCS patients aged 60−64 had a 70 percent higher risk of developing a disability relating to work in the following year compared to 40–44-year-olds [22]. There also appears to be an increased risk of developing cognitive deficits and dementia symptoms with increasing age after surviving COVID-19 infection [23]. Initial findings suggest that PCS patients are moderately to severely limited in their daily activities [24] and that there are particular risk factors for persistent symptoms for those with care and support needs [25].

In addition, reliable data is needed to determine the actual prevalence of PCS as well as more differentiated data on work disability and insights into the coping strategies of PCS patients and their personal perception of care. There is also little analysis of the care providers’ side of the equation.

It is also important to focus analyses on patients with particularly long periods of work disability and/or who are classified as eligible for a defined level of care. It can be assumed that they continue to require adapted care pathways but they have been the subject of hardly any current studies. It is also important to comprehensively examine old and very old PCS patients, their state of health and care trajectories, as well as their prognoses for being classified as needing long-term care.

### Study aims and research questions

The main objective of the LCovB study is to gain a comprehensive understanding of PCS patients’ care trajectories and, based on the results, to derive recommendations for improved healthcare. First, data on the symptoms and care situation of PCS patients will be collected. Second, an expert panel will then use the results to identify key points for optimizing care of PCS patients. A guideline and recommendations for the care of suspected PCS cases, especially for outpatient care, will be developed as long-term goals. Recommendations on disease management will be generated for affected patients.

The following research questions will be examined:

**Main research questions:**

How large is the proportion of persons with the diagnosis PCS (U09.9!)?What are typical healthcare trajectories of PCS patients?

**Further research questions:**

What are the characteristics of persons affected by PCS (main diagnoses; previous illnesses/comorbidities; symptoms/disease burden; socio-demographic characteristics)?Where is the PCS diagnosis most frequently recorded (e.g., in primary care practices)?Which particular features characterize old and very old PCS patients?Which conditions lead to particularly long-term work disability and/or need for care in PCS patients?What regional differences in the healthcare of PCS patients can be identified?What personal view do PCS patients have on their healthcare?What is the long-term care situation of PCS patients, and can care deficits be identified?What improvement measures/potential for PCS patients can be identified from the collected data?

## Methods

The LCovB study is a mixed-methods study in a parallel design with four sub-studies (Modules) (Fig 1).

**Fig 1 pone.0353270.g001:**
[figure not shown]
Study design of the LCovB study.

### Study design

Routine data analyses of statutory health insurance companies (SHI) in Germany from persons with ICD diagnoses U07.1 to U10.9 (Module 1a) and U09.9! (Module 1b) will be carried out (Fig 1). In Module 2, a quantitative, hybrid primary survey of a sample of PCS patients will be conducted. Module 3 consists of semi-structured interviews with PCS patients and Module 4 will involve medical visits and assessments of a sample of severely ill patients. Finally, recommendations for action, including for the care of the seriously ill, will be derived from the findings of the four Modules by an expert panel, based on a Delphi process. The study will be reported based on the Good Reporting of A Mixed Methods Study (GRAMMS) [26]. The analysis of routine data will be carried out in accordance with good practice for secondary data [27]. The guided interviews will be conducted in accordance with the Consolidated Criteria for Reporting Qualitative Research (COREQ) [28]. The Ethics Committee of the Charité – Universitätsmedizin Berlin, Berlin, Germany (Module 1–3: number: EA1/207/24; Module 4: EA4/166/24) has approved the study protocol. No legal or ethical concerns were identified. The data protection policy was approved after explicit verification and consent by the relevant supervisory agencies. The routine data are transferred in anonymized form and in accordance with Section 75 of the German Social Code Book X (SGB X, § 75 SGB X) after approval of the responsible authorities. All participants of Modules 2, 3 and 4 will receive written information about the study objectives, participation, and their right to decline participation and informed consent will be obtained.

### Participants

The following section describes the inclusion criteria of the different data collections.

#### Module 1 (routine data).

The system of company health insurance funds (“BKK”) is a large association of statutory health insurance companies (SHI) in Germany. The 44 participating SHIs represent 7.8 million insured persons and are all members of the BKK Federal Association (BKK Dachverband e.V.). The socio-demographic data of BKK insured persons show that they do not differ significantly in their characteristics or structure from the respective reference population of all SHI insured persons in Germany. In the BKK insured population, the genders are almost equally represented. The average age is 43.0 years. Half of the BKK insured individuals (49,6%) are employed; 22.7% are family members; 19.8% are retired. In terms of age, gender, and occupational characteristics, employed BKK members do not differ significantly from all employees subject to social insurance contributions in Germany. The only exception is that a higher proportion of BKK members are employed in manufacturing-related occupations, as company health insurance funds are traditionally found primarily in companies in the manufacturing or processing industries. The regional distribution of employed BKK members largely corresponds to that of all employees subject to social insurance contributions in Germany; they are more commonly found in economically strong federal states such as Bavaria [29].

Routine data will be examined of persons who were continuously insured with one of the SHIs participating in the LCovB project from 01.01.2021 to 31.12.2023 (Module 1b: 01.01.2021 to 31.12.2024). In addition, the insured persons must be at least 18 years old at the beginning of the quarter in which the initial diagnosis (outpatient or inpatient) was documented. The two Modules follow different research objectives. Module 1a aims to examine the prevalence of PCS in relation to other diagnoses. Therefore, in the first data delivery for Module 1a, all insured individuals with ICD codes U07.1, U07.2, U08.9, U09.9!, and U10.9 are included. Module 1b focuses on the care trajectories of patients with PCS. Therefore, in the second data delivery for Module 1b, the diagnosis U09.9! serves as the inclusion criterion.

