#### Module 2 (survey).

For the standardized survey, a random sample of insured persons of two participating health insurance funds (Pronova BKK and mkk – meine Krankenkasse) are contacted who are aged 18 years or older and for whom the diagnosis U09.9! was documented in the quarter available at the time of the survey with a complete database and at least one other quarter in the previous three quarters (M2Q criterion) [30]. Exclusion criteria are: deceased, not continuously insured during the above-mentioned period, has refused contact by SHI or the use of data for research purposes, lives abroad, has a protection mark (e.g., employee).

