## Discussion

The aim of the LCovB study is to identify the specific implications for healthcare and to address the still deficient research and data situation on the post-COVID disease field. This will be realised through a comprehensive mixed-methods analysis integrating multiple data sources. Currently, there are no evidence-based, causal treatment options. These are limited to symptom-oriented therapeutic approaches. PCS patients experience significant barriers to accessing healthcare, often related to insufficient medical support and knowledge, lack of recognition and the stigmatization of the disease [11,48–51], which makes it all the more important to improve care pathways.

Using routine data, the care trajectories of diagnosed PCS patients will be analysed. The broad recruitment base allows for the tracking of different care pathways based on the respective diagnosis. This enables the analysis of deficits, over- and undercare, inappropriate care, as well as the identification of best practices. The project also explicitly incorporates the perspectives of PCS patients and self-help groups. Further, insights will be generated into the specific disease situation and care situation for selected affected groups: the seriously ill, the elderly, and patients who become dependent on care as a result of a post-COVID illness. The analyses will form the basis for the development of recommendations and guidelines for care (particularly for practising physicians) and self-management (for patients) specifically targeted at the aforementioned affected groups. These recommendations, based on the insights of a multidisciplinary expert panel, will contribute to the development of needs-based care pathways that more quickly refer affected individuals to the appropriate setting. The research findings will also contribute to strengthening the evidence for necessary changes so that care structures can be further expanded in line with needs (e.g., adapting care services, reintegration into working life). Furthermore, the project results can contribute to the further development of the existing S1 guideline for post-COVID/long-COVID.

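### Module 1 requires continuous insurance to a fixed end date, so as written it drops patients who die after diagnosis but before that date, which matters for the old and care-dependent

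*Protocol article*

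**What the plan says.** Under Participants, Module 1 (routine data), the Protocol article includes "persons who were continuously insured with one of the SHIs participating in the LCovB project from 01.01.2021 to 31.12.2023 (Module 1b: 01.01.2021 to 31.12.2024"). The age criterion refers to a diagnosis at some point within that period: a person must be "at least 18 years old at the beginning of the quarter in which the initial diagnosis (outpatient or inpatient) was documented". The section gives no exception for death. Table 1 (Data collection) lists the variables for both deliveries, including care level, but no death or exit variable.

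On purpose, the same section says that "Module 1b focuses on the care trajectories of patients with PCS". The Introduction asks for old and very old patients to be studied, including "their prognoses for being classified as needing long-term care". The further research questions include "Which particular features characterize old and very old PCS patients" and "Which conditions lead to particularly long-term work disability and/or need for care in PCS patients". The Discussion names as target groups "the seriously ill, the elderly, and patients who become dependent on care as a result of a post-COVID illness".

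The Discussion's limitations cover the lack of individual linkage, coding quality, time lag and recall. They do not mention selection on survival.

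**The concern.** A calendar window fixed in advance is harmless when it lies before the index event. Here the index diagnosis lies inside the window, and the person must stay insured until it closes. Death ends insurance, so the cohort is selected on surviving the period in which its outcomes are measured. The required survival also varies: up to four years in Module 1b for a diagnosis at the start of 2021, and almost none for one at the end of 2024.

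Four results are at stake:

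- **Need for care.** A prognosis for care need is estimated only in people who lived to the end of the window.
- **Care and costs.** The last phase of life is absent for everyone who died inside the window.
- **Comparisons by age and diagnosis date.** The share removed rises with mortality and with time to the window end, so older groups and earlier diagnoses are filtered more strongly.
- **The PCS proportion in Module 1a.** People who died after acute COVID-19 drop out of the population behind the proportion, and people with PCS who died drop out of its numerator.

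No other module fills the gap. Module 2 rules out the deceased ("Exclusion criteria are: deceased, not continuously insured during the above-mentioned period"), as a postal survey must, and Modules 3 and 4 recruit living people.

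**Working it through.** **Inputs from the Protocol article.** The window ends on 31.12.2023 (1a) and 31.12.2024 (1b), and both windows start on 01.01.2021. The article gives no figure for deaths among PCS patients, so there is no stated value to reproduce. Its only death count concerns all infections: 188,000 / 39,000,000 = 0.48%. That says nothing about mortality after a PCS diagnosis by age or care level.

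**Assumption.** Annual mortality m after diagnosis is 0.3% for working ages and 5% to 10% for old or care-dependent patients, with 20% as an extreme. None of these rates comes from the documents.

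**Step 1: share removed by death.** With t years from diagnosis to the window end, the share removed is 1 − (1 − m)^t.

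| Assumed m | 1b, diagnosis mid-2022 (t = 2.5) | 1b, diagnosis start of 2021 (t = 4) | 1a, diagnosis start of 2021 (t = 3) |
|---|---|---|---|
| 0.3% | 0.7% | 1.2% | 0.9% |
| 5% | 12.0% | 18.5% | 14.3% |
| 10% | 23.2% | 34.4% | 27.1% |
| 20% | 42.8% | 59.0% | 48.8% |

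Example: 1 − 0.90^2.5 = 0.232.

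**Step 2: dependence on diagnosis date.** At m = 10% in Module 1b, the share removed is 10.0% with one year to the window end, 19.0% with two years and 34.4% with four. Patients of equal prognosis are filtered differently according to when they were diagnosed.

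**Step 3: direction for need for care.** Take three states (no care, care, dead) with care onset rate a, mortality μ0 without care and μ1 with care, over t = 3.5 years. In the full cohort, cumulative care onset is a/(a+μ0) × [1 − exp(−(a+μ0)t)]. Among survivors, the share in care is C/(H+C), where H = exp(−(a+μ0)t) and C = a × [exp(−μ1 t) − exp(−(a+μ0)t)] / (a+μ0−μ1).

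| a, μ0, μ1 per year (assumed) | Died | Care onset, full cohort | In care, survivors only |
|---|---|---|---|
| 0.15, 0.05, 0.25 | 26% | 37.8% | 32.5% |
| 0.10, 0.05, 0.20 | 22% | 27.2% | 24.3% |
| 0.15, 0.10, 0.10 | 30% | 35.0% | 40.8% |

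First row: 0.75 × (1 − exp(−0.7)) = 0.378; H = 0.497, C = 0.239, and 0.239/0.736 = 0.325.

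Where care-dependent patients die faster, the survivors-only figure is too low. Where mortality is equal in both states, it is too high, because survivors had the whole period in which to reach care. The distortion exists in each of these cases, but its sign depends on rates that the article does not give.

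**The case against.** The strongest reply is that the exclusion of decedents is inferred. The article is condensed, a data specification not shown may treat death as a valid end of insurance, and Table 1 lists data domains, so a missing death field there is weak evidence. The Module 2 criteria list the deceased separately from those not continuously insured, which suggests that the authors may distinguish the two. Module 1 is also described as a complete collection. This lowers certainty about what will be delivered, but it does not change the stated rule, which is unqualified. The Module 2 criteria do not govern Module 1. If decedents are in fact kept, the text needs to say so.

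A second reply concerns weight. Old age and care need are further research questions, the only regression outcome named for Module 1 is incapacity for work, and the insured population has a mean age of 43.0 years with 19.8% retired. This stands for working-age results, where the loss is about 1%. It does not answer the point for the groups that the Discussion singles out.

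Observing everyone for the full window is a recognisable choice when complete trajectories and costs are compared. It then describes survivors, and the article does not say so.

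A reader might infer that the severely ill are seen only through this filter. That goes too far: Module 4 examines about 15 housebound patients, and the insurance criterion does not apply to it.

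**Conclusion.** The point holds for Module 1 as written: persons who die after diagnosis but before 31.12.2023 (1a) or 31.12.2024 (1b) fail the inclusion rule. The loss is probably negligible at working ages (about 1% at an assumed 0.3% per year). It can be material for the old, very old and care-dependent (about 12% to 34% at an assumed 5% to 10% per year over 2.5 to 4 years).

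Three stronger readings are not supported:

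- **That every patient who died is removed.** Deaths after the window end are kept.
- **That results will be too favourable.** The survivors-only share in care can lie below or above the full-cohort figure. In Module 1a, losing people who died after acute COVID-19 could raise the PCS proportion, while losing PCS decedents lowers its numerator.
- **That around half of the very old are lost.** The 43% to 59% figures for Module 1b need an assumed 20% annual mortality, and 59% also needs a diagnosis at the very start of the window.

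**What to change.** 1. Change the Module 1 criterion to: continuously insured from 01.01.2021 until 31.12.2023 (Module 1b: 31.12.2024) or death, whichever comes first.
2. Add quarter of death to both extractions and list it in Table 1.
3. In analyses of need for care after diagnosis, treat death as a competing event when cumulative probabilities are reported, or censor at death when rates are reported.

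**Cost.** This is one changed selection rule and one added variable, applied across the 44 insurers, with no new data collection from patients. Transfers need approval by the responsible authorities, so an addendum to the data-protection approval may be required. Under Status of the study, extraction is expected to be completed by May 2026. If a delivery has already been made, a supplementary delivery of decedents would serve.

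**If decedents cannot be obtained.** State in the limitations that Module 1 results, especially for the old and care-dependent, apply only to persons who survived to the window end. If the unpublished data specification already keeps decedents, correcting the criterion's wording and Table 1 is enough for steps 1 and 2.
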